### Compensation

Study participants are not given financial compensation for their time, but they are given $5USD towards transport expenses for data collection appointments. Transport for intervention patients clinical appointments (of which there are at least two more than research appointments) are not reimbursed as this may influence the outcome. For comfort, participants are given a drink and small snack on arrival for their data collection appointments.

### Ethical considerations

Ethical approval has been sought and secured from Kings College London Research Ethics Committee (BDM/10/11-31), University of Cape Town (019/2011), Ministry of Health of the Western Cape (Research request ID: 10252) and Kenyan Medical Research Institute (KEMRI/RES/7/3/1).

A distress protocol will be used, with participants being offered the opportunity to cease the interview if they become distressed during questioning. They will be able to decide to restart or abandon the interview at their own discretion. All information gathered during data collection will be confidential, except in the situation of a participant or someone related to the participant being at risk, in which case the information will be acted upon. Please see Figure 1 for study flow chart.

**Figure 1 F1:**
[figure not shown]
Study flow chart.

### Data collection and analysis

Data will be collected by local researchers following the study protocol. They will be trained in quantitative and qualitative data collection methods, and will receive specific training for each tool used in this study.

### Tools

The data collection tools are:

#### Patient demographic record

##### Administered once only, at month 0

This brief record will be used to record age, gender, couple status, number of children, number of financial dependents, education, recent CD4, date of ART initiation, WHO staging data and whether the patient is receiving TB treatment. This questionnaire also includes assessment of relative socioeconomic status, as used in the Demographic Health Surveys [42].

#### APCA AFRICAN POS (10 items)+ eastern Co-operative global performance scale (ECOG) (1 item)

##### Administered at months 0, 1, 2, 3 and 4

The original Palliative Outcome Scale (POS) was developed at King’s College London [43,44] (further information and resources are available at http://pos-pal.org/). The APCA African POS was culturally adapted from the original POS during development in ten centres in six sub-Saharan African countries [45]. The ten items of the APCA African POS address the primary physical, emotional and spiritual concerns of patients and families with progressive disease using a scoring method appropriate for a range of literacy skills. Each item is scored on a scale of 0–5, and can be scored verbally or using the “hand” method commonly used in Africa. Using this method, a closed fist represents “0”, moving up to an open hand scoring “5”. These methods have been validated among 300 patents under palliative care in Africa with a correlation of around 0.9 for verbal vs hand scoring methods for both pain scores and symptom scores. For those with no family carer, family items are scored as “0”, i.e. no problem [45]. The tool is sensitive to change and acceptable to patients, family and staff. Its brief nature makes it highly appropriate for use in a large-scale longitudinal study [46].

The ECOG is a single item measure of performance and is the most widely used performance measure [47]. Scores range from 0 (normal activity) to 4 (unable to get out of bed). It has been used in previous work amongst HIV positive people in Africa [48].

#### Medical outcome study -HIV (MOS-HIV quality of life measure)

##### Administered at months 0, 1, 2, 3 and 4

The MOS-HIV was originally developed as a general health questionnaire in the USA [49]. A modified HIV-specific version was developed and widely used. It has been culturally adapted to the Ugandan HIV setting [50] and has been used in Rwandan [51] Zimbabwean [52] and Ugandan populations [53]. The 35 items address the domains of role function, pain, physical functioning, cognitive functioning, social functioning, general health perception, mental health, health distress and vitality.

#### General health questionnaire-12 (GHQ)

##### Administered at months 0, 1, 2, 3 and 4

The GHQ-12 is a widely used measure of psychological morbidity [54]. It is the shortest validated version of the original GHQ, which was a 60-item instrument when it was first designed in the 1970s [55]. The GHQ-12 has been translated and validated into many languages including Kenyan Kiswahili [56].

#### Adherence and risk questionnaire

##### Administered at months 0, 2 and 4 only

The adherence and risk questionnaire has been used for research in the UK, predominately with gay men [10,57]. The risk section of the questionnaire consists of three questions detailing sexual partners in the past four months, detailing unprotected sex and unprotected sex with people of unknown HIV status. The adherence questions asks participants how many ART doses they have missed in the past week.

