#### Outcomes

The primary outcome is self-reported pain after four months. The secondary outcomes are health-related quality of life; adherence to treatment; risk behaviours; and psychological morbidity and the core domains of palliative care as defined by the WHO (physical, psychological, social and spiritual well-being) as measured by the APCA African POS.

Patients will be followed up for four months and most outcomes are measured at baseline and monthly intervals, described below.

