### Randomisation

Consenting patients will be administered the initial assessment and subsequently randomised to intervention or control group. This is done using block randomisation to ensure a manageable work load for the nurse delivering the intervention, with 40 per block. Each study site has been issued with three sealable pots containing 20 pieces of paper with “I” for intervention and 20 pieces of paper with “C” for control. Once a piece of paper has been blindly selected by the researcher, the patients is informed whether they are in the control or intervention group and this is recorded on a form which is kept separately from the data collection tools and records. The piece of paper is discarded and the process continues until the pot is finished, when the next pot is then used. The allocation to control or intervention is not blinded as it would be impossible to maintain this blinding when the intervention was delivered.

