### Quantitative data collection

Data collection will be conducted in the usual place of care, i.e. at home or at the clinic. For all tools, data will be collected as close as possible to the monthly timetable, with a two week grace period either side. Data collection appointments will be co-ordinated with clinical appointments where possible for minimal patient disruption.

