### Analysis

#### Quantitative analysis

Data will be described in two stages:

1) Cross sectional baseline analysis: descriptive analysis of demographic and clinical variables, baseline primary and secondary outcomes for the two groups (standard care and palliative care). Continuous variables will be presented as mean (standard deviation), median (range); categorical variables will be described as proportions. Baseline scores for primary and secondary outcome variables for two groups will be compared using two-sample t-test (or Mann–Whitney U test if non-normal distribution) for continuous data and Chi square test for categorical data.

2) Summary measures: change in primary and secondary outcomes from baseline to the final time point will be summarized, using paired t-tests or the non-parametric equivalent.

Longitudinal analysis will be performed to address the primary study objectives of comparing pain and other symptoms, (objective 1) and subsequently adherence (objective 2), health related quality of life (objective 3) and multidimensional palliative care outcomes such as psychological and spiritual well-being (objective 4), in the intervention and control groups. Factors of the APCA African POS were identified from APCA POS data from similar samples (high prevalence of HIV) in Sub Saharan Africa [60]. Three factors were identified which covered 1) physical and psychological symptoms, 2) interpersonal dimension and 3) the existential dimension. They will be analysed for differences between intervention and control groups. For continuous outcomes, the change in scores for two groups will be compared using general linear model with adjustment of baseline differences and covariates (demographics and clinical variables). For categorical outcomes, the two-group comparisons will be implemented using generalized linear model and adjusting for design effects, the repeated measures will be taken into account using generalized estimating equations (GEE) technique.

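### About half of the four-month recall window for the month-2 risk questions precedes randomisation, so month 2 should not enter the treatment-effect estimate for risk behaviours; the month-4 comparison is sound when on schedule

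*Protocol article*

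**What the plan says.** All references are to the protocol article.

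- **Outcomes** names risk behaviours as a secondary outcome: "The secondary outcomes are health-related quality of life; adherence to treatment; risk behaviours". It also fixes the length of follow-up: "Patients will be followed up for four months". It sets a four-month time point for pain but none specifically for risk behaviours.
- **Adherence and risk questionnaire** describes the risk items: "The risk section of the questionnaire consists of three questions detailing sexual partners in the past four months". The schedule is "Administered at months 0, 2 and 4 only". The four-month window is explicit for the sexual-partners question. The two unprotected-sex questions follow in the same sentence without a window of their own. The adherence item in the same questionnaire looks back one week.
- **Randomisation** places allocation after baseline: "Consenting patients will be administered the initial assessment and subsequently randomised to intervention or control group".
- **Quantitative data collection** allows visits to vary, "with a two week grace period either side".
- **Quantitative analysis** promises a summary of change from baseline to the final time point for primary and secondary outcomes, and a longitudinal analysis for objectives 1 to 4. For categorical outcomes it adds that "the repeated measures will be taken into account using generalized estimating equations (GEE) technique". It does not say how the month-2 risk answer is used.

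**The concern.** Behaviour before randomisation cannot be changed by the allocated treatment. A four-month question asked two months after randomisation mixes two months that treatment cannot affect with two that it can. The first two were already reported at baseline; the last two are reported again at month 4. If the month-2 answer is treated as an ordinary post-treatment measurement, the difference between arms at that visit is too small, and so is any effect averaged over months 2 and 4.

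The recall wording and the visit schedule are data-collection choices, so this is not something that a statistical analysis plan can fully repair. Once a single four-month answer has been recorded, no model can split it at the date of randomisation; the analyst can only set the month-2 answer aside.

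**Working it through.** **Plan's own figures.** The article gives no effect size, power or event rate for risk behaviours, so there is no figure for this outcome to reproduce. The only sample-size step that can be rebuilt is the attrition allowance: 56 / (1 − 0.06) = 59.6, rounded up to 60 per arm, as stated.

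**Inputs.** Recall window 4 months; visits at months 0, 2 and 4; randomisation at about month 0; visit tolerance two weeks, taken as 0.5 month.

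**Windows on schedule, in months from randomisation.**

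| Visit | Window | Share before randomisation |
|---|---|---|
| Month 0 | −4 to 0 | 100% |
| Month 2 | −2 to +2 | 50% |
| Month 4 | 0 to +4 | 0% |

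**Effect of the grace period.** For a visit t months after randomisation, the share before randomisation is max(0, 4 − t)/4.

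- Month 2, two weeks early: (4 − 1.5)/4 = 62.5%
- Month 2, two weeks late: (4 − 2.5)/4 = 37.5%
- Month 4, two weeks early: (4 − 3.5)/4 = 12.5%
- Month 4, on time or late: 0%

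**Effect retained, counts.** Assume a count that adds up over time and a treatment effect on its rate that starts at randomisation and stays constant. The fraction retained is then the post-randomisation share of the window: 0.50 at month 2 and 1.00 at month 4. An equally weighted average retains (0.50 + 1.00)/2 = 0.75.

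**Effect retained, yes/no items.** Let a and b be the probabilities of no event in two months under treatment and control, with independent events at constant rates.

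- Month-4 risk difference: (1 − b²) − (1 − a²) = (a − b)(a + b)
- Month-2 risk difference: (1 − b·b) − (1 − b·a) = b(a − b)
- Ratio of month 2 to month 4: b/(a + b)

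The ratio is below 0.5 if treatment lowers risk (a > b), close to 0.5 when events are rare, and above 0.5 if treatment raises risk.

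**Illustration of power (assumed, since the article gives none for this outcome).** Take an effect that would have 80% or 90% power undiluted with 56 per arm, two-sided 0.05, and the same variance throughout. If f is the fraction of the effect retained, power is Φ(f × (1.960 + z) − 1.960), where z is 0.842 for 80% and 1.282 for 90%.

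| Effect retained | Power if 80% undiluted | Power if 90% undiluted |
|---|---|---|
| 100% | 80% | 90% |
| 75% | 56% | 68% |
| 50% | 29% | 37% |

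**The case against.** The strongest reply is that the design fits where it matters most. Follow-up lasts four months, so the month-4 window is exactly the post-randomisation period and adjoins the baseline window without overlap. The one analysis sentence that clearly reaches every secondary outcome concerns change from baseline to the final time point. Risk behaviour is absent from the numbered objectives and from the list that the longitudinal analysis is said to address. The GEE sentence concerns categorical outcomes and does not say that visits are averaged; a model with visit-specific effects would leave month 4 intact. Choice of model terms is commonly left to a statistical analysis plan, which is not shown.

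Most of this stands, and it limits the point. A reader might infer that the treatment effect on risk behaviours is diluted as a whole. The documents do not support that, because the on-schedule month-4 contrast is unaffected. A reader might also count the shared two months between the month-2 and month-4 answers as a second bias. That overlap mainly adds within-person correlation, which GEE accommodates.

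Two things remain. The baseline-to-final sentence describes a summary with paired tests, not a comparison between arms. And the general GEE sentence, read as written, lets months 2 and 4 both enter the group comparison of a categorical risk item; nothing excludes month 2 or makes month 4 decisive.

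**Conclusion.** The point holds in a limited form. The month-2 risk answer is a poor post-treatment measure: about half of its window precedes randomisation (37.5% to 62.5% with the grace period). The month-2 contrast, and any estimate that pools it with month 4, is biased towards no effect. The month-4 answer is not diluted on schedule and carries 12.5% pre-randomisation time if taken two weeks early.

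The window shares follow directly from the stated schedule. The retained effects of 50% and 75% are conditional: they need behaviour that adds up over time, an immediate constant effect and, for the 75%, equal weighting of visits. Numbers of distinct partners do not add up in this way, since one stable partner counts once in any window. Extending the window to the two unprotected-sex questions is a reasonable reading of the sentence, not an explicit statement.

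This is minor: one secondary outcome is involved. Pain is unaffected, and so is adherence, with its one-week recall.

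**What to change.** Do not ask the risk items at month 2. If they are asked, or have already been collected, keep month 2 out of the treatment-effect estimate and report it descriptively. In either case, state that risk behaviours are analysed by a between-arm comparison at month 4, adjusted for the month-0 answer. State the recall window for each of the three questions.

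This costs one or two sentences in the analysis section. It needs no rewording or retranslation of the items, and dropping them at month 2 spares participants sensitive questions. The only loss is a month-2 reading that cannot be cleanly interpreted as a treatment effect.

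An alternative is a two-month recall at all three visits, which matches the visit interval and gives 0% pre-randomisation time at months 2 and 4 on schedule. It is more debatable: it changes the wording and translations of a questionnaire used before, loses comparability with that earlier use, and captures fewer events per window with about 56 patients per arm.

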#### Client services receipt inventory (CSRI)

##### Administered at months 0, 1, 2, 3 and 4

The CSRI aims to explore the components of care received by patients. The version of the CSRI used in this study is based was adapted from versions used in other palliative care research and adapted for use in Africa [58,59]. The version used for this study has been simplified in that instead of documenting time, the researcher records whether the client has received a service or not as a binary outcome.

#### Qualitative interview schedule

##### Administered for selected patients at month 4

The interview schedule was developed in collaboration with international researchers experienced in HIV and palliative care research and local researchers with an in depth knowledge of the delivery of palliative care at the study sites. It is designed to explore the intervention and control patients’ perspectives on participating in a randomised trial, the intervention patients’ experiences of receiving palliative care, and to determine the potential mechanism of action of the intervention.

### Piloting

All tools were professionally translated into local languages and checked for consistency and accuracy by local researchers in each country and piloted with 35 patients in Kenya. This checked for clarity of questions, time required for data collection, patient burden and availability of requested information.

### Quantitative data collection

Data collection will be conducted in the usual place of care, i.e. at home or at the clinic. For all tools, data will be collected as close as possible to the monthly timetable, with a two week grace period either side. Data collection appointments will be co-ordinated with clinical appointments where possible for minimal patient disruption.

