#### Control

Patients randomly allocated to the control arm will receive the usual clinical care delivered by the HIV clinic. Nurses who have had no exposure to palliative care will provide this service.

In Kenya this consists of six-monthly clinical assessments once ART has been established, with investigations and treatment for any relevant symptoms or problems. Patient may attend the clinic for medications refill only or may request more frequent appointments if they experience a problem. In South Africa, patients attend the public hospital monthly for a brief appointment to refill medications. They may present for additional appointments as necessary.

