### Minimum package of palliative care

Patients allocated to the intervention arm will receive an initial clinical assessment , followed by either one further visit or phone call within the first week, one further visit or phone call within the second week and one visit per month thereafter. The focus of the care provided will be on holistic assessment and management of physical, psychological, spiritual and social problems. This minimum package of care can be supplemented by additional clinical support as required on a case-by-case basis.

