### Data management and quality assurance

A researcher will be employed at each participating centre. This person will be responsible for managing recruitment, data collection and data entry. Fortnightly study team conference calls will be used to ensure that all queries are promptly resolved, attended by all members. All quantitative data will be double-entered into purpose designed EpiData databases. Discrepancies will be resolved by referring back to the original questionnaires.

Following data checking and cleaning, the data will be imported into Stata for analysis at KCL. Qualitative transcripts will be imported into NVivo (version 9) for analysis. All hard data will be stored for at least seven years in accordance with the UK Data Protection Act 1998.

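### Pain interviews are tied to clinical appointments with no order set between interview and consultation, and the interviewer apparently knows the arm; in Kenya, interview circumstances can differ by arm

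*Protocol article*

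**What the plan says.** All references are to the protocol article.

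- **Outcome.** The Outcomes section states: "The primary outcome is self-reported pain after four months". Pain is an item of the APCA African POS, scored 0–5 by voice or hand signal. The POS is "Administered at months 0, 1, 2, 3 and 4", in both arms.
- **Who knows the arm.** Under Randomisation the researcher draws the allocation: "Once a piece of paper has been blindly selected by the researcher", after which the patient is told the result. On blinding, the section says: "The allocation to control or intervention is not blinded as it would be impossible to maintain this blinding when the intervention was delivered". Data management and quality assurance provides for a researcher at each centre and adds: "This person will be responsible for managing recruitment, data collection and data entry".
- **When and where interviews happen.** Quantitative data collection sets a monthly timetable with two weeks' grace either side, at home or at the clinic. It then adds: "Data collection appointments will be co-ordinated with clinical appointments where possible for minimal patient disruption".
- **Clinical visits, intervention arm.** After the initial assessment and a contact in week 1, Minimum package of palliative care gives "one further visit or phone call within the second week and one visit per month thereafter".
- **Clinical visits, control arm.** For Kenya, the Control section says: "In Kenya this consists of six-monthly clinical assessments once ART has been established". It also allows attendance only to collect medication, and extra appointments on request. Settings describes regular Kenyan nurse appointments whose frequency varies with the patient's condition and adherence. South African controls attend monthly.

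**The concern.** A 0–5 pain score given aloud or by hand to an interviewer can shift without any change in pain. Two features of the plan could cause such a shift.

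First, the reason given for not blinding concerns delivery of care. It explains why patients and nurses know the arm, but not why the person recording the pain score must know it. Keeping the allocation form apart from the data tools does not blind the researcher who drew the paper.

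Second, the scheduling rule reads the same for both arms but works through clinical visits, and the arms do not have the same visits. An intervention patient nominally always has a monthly palliative visit with which the interview can be paired, and nothing stops the interview from following a supportive consultation. A Kenyan control may have no comparable visit that month, and would then be interviewed on a separate day or at home.

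The baseline interview precedes randomisation, so any such shift arises only afterwards. It would enter the month-4 comparison directly, and adjusting for baseline would not remove it.

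**Working it through.** **1. Is the same interviewer involved?** The researcher draws the paper (Randomisation), and the centre's researcher manages recruitment and data collection (Data management and quality assurance). The latter section says the researcher manages data collection, and Data collection and analysis speaks of local researchers in the plural. That the person who drew the paper takes every interview is therefore a strong inference, not an explicit statement. No masked assessment is described for either trial.

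**2. How far can interviews be paired with clinical visits?**

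| | Clinical contact during follow-up | Scope for pairing a monthly interview |
|---|---|---|
| Intervention, both countries | Monthly after the second week | Nominally every month |
| Control, South Africa | Monthly refill appointment | Nominally every month, with usual care |
| Control, Kenya | Six-monthly assessment, plus refill, requested or variable nurse visits | Uncertain |

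For Kenyan controls, take the six-monthly assessment alone and assume that it falls at a random time. The month-4 window is 4 weeks (28 days) wide and the cycle is 365.25/2 = 182.6 days. The chance that the assessment falls in the window is 28/182.6 = 0.153, about 15%. It would be near 0% for a patient recruited at such an assessment. Refill, requested or regular nurse visits would raise it by an amount that cannot be worked out from the article, because Control and Settings describe the Kenyan schedule differently.

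**3. The plan's own sample size.** 56/(1 − 0.06) = 59.6, rounded up to 60 per arm, as stated. The 56 itself cannot be reproduced, because the article gives neither SD nor power.

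**4. Implied SD.** With a 1-point difference, two-sided 5% and n = 56 per arm, SD = √(56/2) / (z₀.₉₇₅ + z_power):

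- 80% power (assumed): 5.292/(1.960 + 0.842) = 1.89
- 90% power (assumed): 5.292/(1.960 + 1.282) = 1.63

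**5. Error rate if pain is truly equal but its measurement is shifted by b points.** SE = SD × √(2/56), which is 0.308 for SD 1.63 and 0.357 for SD 1.89. The chance of p < 0.05 is 1 − Φ(1.96 − b/SE) + Φ(−1.96 − b/SE).

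| Assumed bias b | SD 1.63 | SD 1.89 |
|---|---|---|
| 0 | 5.0% | 5.0% |
| 0.10 | 6.2% | 5.9% |
| 0.25 | 12.8% | 10.8% |
| 0.50 | 36.8% | 28.8% |

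For example, with SD 1.89 and b = 0.50, b/SE = 1.40 and 1 − Φ(0.56) = 0.288. The article gives no basis for choosing among these values of b. The largest is half of the 1-point change that it treats as clinically significant.

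**The case against.** The strongest reply is that the plan treats the arms alike: same instrument, same months, same two-week window and same rule on place. Co-ordination with clinical visits applies only where possible and within the monthly timetable. This stands. A reader might infer that pain is in fact measured differently by arm, but the documents do not support that. They leave room for a difference without fixing one.

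A reader might also infer that Kenyan controls usually have no visit to pair with. That is not supported either. Refill and requested visits, and the regular nurse appointments described under Settings, make the gap uncertain. The visit-frequency argument does not extend to South Africa, which is a separate trial with monthly control attendance.

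There are partial safeguards. The allocation form is kept apart from the data tools, researchers are trained in minimising bias, and both arms receive the same transport money and snack at data-collection appointments. They are worth having, but none governs the order of interview and consultation or masks the researcher who drew the paper.

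It may also be said that interview order belongs in a field manual and is no omission from an article. That is fair for detail left out. Here, however, the article states a rule linking interviews to clinical visits, and the concern is what that rule permits.

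Finally, the patient knows the arm and supplies the score, so no change to the interview removes all the bias of an open trial. The error rates above come from an unadjusted comparison, whereas the Analysis section plans an adjusted model. They illustrate sensitivity and do not predict the trial's error rate.

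**Conclusion.** The point holds as a risk. In both trials the pain interviewer is apparently aware of allocation, and the scheduling rule lets the score be taken after a palliative consultation. In Kenya the same rule can also make interview circumstances differ by arm. How often that would happen depends on a control visit schedule that the Control and Settings sections describe differently and that must be reconciled.

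The size is unknown. An assumed bias of 0.10 points barely matters (about 6% against a nominal 5%), 0.25 gives 11–13%, and 0.50 gives 29–37%. These figures rest on an SD back-solved at an assumed 80 to 90% power and on bias values without a source in the documents. Quoting only the 0.50 row would overstate the case.

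This is a cheap improvement worth making to protect a subjective primary outcome. It does not show that the trial's result would be invalid.

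**What to change.** Amend Quantitative data collection so that, in both arms:

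1. the POS pain item is asked first at each interview, before any clinical contact on the same day;
2. the month-4 interview follows one scheduling rule and one location rule, with home interviews kept as a fallback so that primary data are not lost.

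Reconcile the descriptions of Kenyan usual-care visits in Control and Settings, so that the scope for pairing can be judged.

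State as a limitation that interviewers are not masked. Masking should not be claimed as achievable with the present staff. Even if someone else drew the allocation, the service-receipt inventory is given every month and would reveal the arm to the same interviewer before month 4, wherever it came in the interview. Real masking would need an additional interviewer, and patients could still disclose their arm.

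Items 1 and 2 need only a change of wording and no extra staff. The cost is slightly tighter patient flow on visit days. Sample size, treatment and analysis are unaffected.
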